**Motivation**

Previous work suggests that a greater interest in a task relates to higher task performance [46]. The contribution of motivation in within-subject differences can be examined by comparing and contrasting the predictive role of (subjective) interest in each task. If motivation or enjoyment play a key role in governing variability, we would expect that a subjective assessment of ‘most to least fun’ task would correspond to a similar, scaled ordering of variability. Previous findings found that motivation was task independent [47]. However, whether their enjoyment for a task impacts their fluctuations in the task performance is poorly understood, and will be examined in this study.

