**Fig. 2 Fig2:**
[figure not shown]
Working memory task procedure. Participants are presented with a shape of dots (e.g., triangle), after which a sequence of dots turns yellow sequentially. Participants are instructed to copy the sequence in the same order

*Fluid reasoning:* to measure fluid reasoning, we use a matrix reasoning task similar to Raven’s Progressive Matrices [101, 102] or Cattell’s Culture Fair test [103]. As existing tests are proprietary (precluding reuse by others with fewer means), and even open source alternatives, e.g. MaRs-IB, [104] have a limited number of items, we developed our own battery of items. To do so, we adapted an existing pipeline [102] and generated 3-by-3 grids with elements varying across five dimensions: shape, colour, size, number and orientation. Crucially, item difficulty is modified following the rules outlined in Carpenter et al. [101]. During the task, participants see a 3 by 3 grid from which all cells contain one or more elements, except the bottom right cell, which is left empty. Participants are asked to select, out of 4 options, which option best fits this empty cell of the grid (see Fig. 3). In the behavioural arm of the study, there is a time limit of 30 s on the response. In the deep phenotyping arm, participants perform the same task with either low time constraints (30 s to respond) or high time constraints (10 s to respond) (see CODEC-MRI: imaging procedure). After each response, the correct answer is outlined in green. After finishing all items in a block/session, participants see their total score (number of correct answers) on the screen.

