**Fig. 3 Fig3:**
[figure not shown]
Fluid reasoning task procedure for 2 example trials. Participants are presented with a 3-by-3 grid. Each cell contains one or more elements, except the bottom right cell. Participants are instructed to decide which out of four response options fits best in the empty cell

*Processing speed:* to measure processing speed, we use a version of the classic ‘Whack-a-Mole’ game. Participants view a (digital) grass field, with a cartoon mole appearing at unpredictable locations on an invisible 3-by-3 grid (see Fig. 4). The participants’ task is to tap the moles as quickly as they can, before they disappear. Moles are presented on the screen one by one with a total of 10 mol per trial. A mole disappears once it is pressed or after 2000ms. A new mole appears at an interval selected randomly between 1000 and 2000ms. To prevent children from clicking randomly, clicking on an empty section of grass will cause a mole to disappear without gaining points.

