**Fig. 4 Fig4:**
[figure not shown]
Whack-a-mole task procedure. Participants are presented with a digital grass field. Per trial, 10 mol will appear sequentially. Participants are instructed to tap the appearing mole as quickly as possible

Participants are awarded points for both accuracy and speed. Feedback on total score and speed is provided after each series of 10 moles. Besides accuracy and reaction time, data collected includes the location of the finger press, calculated on a 9-by-9 invisible grid underlying the grass field. This enables the calculation of distance between the mole and the actual finger press with greater accuracy.

*Vocabulary:* In order to measure vocabulary, we use a multiple-choice vocabulary task (see Fig. 5) based on the online learning platform Taalzee [105, 106]. We sample a set of 2000 words and alternatives previously used and validated in Taalzee. In the first half of the task, participants see a word and are asked which of five alternatives best fits the description of the word. In the second half of the task, participants are asked which of five alternatives best fit the opposite meaning (antonym) of the word. The order of the five alternatives is randomised at each round and the correct answer is provided after each exercise. Participants receive points for accuracy and speed. There is no time limit on each trial, however, after a series of 5 answers with a reaction time under 750 ms - suggestive of guessing - the participant is instructed to slow down.

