#### Key hypotheses

**Aim (1) reliably measure individual differences in cognitive variability across timescales and tasks:** to overcome previous challenges in reliably measuring variability, we first use DSEM to estimate individual differences in variability across task domains (between the various tasks we assess), and across levels of temporal resolution (from trial-to-trial, across sessions within days, from day-to-day and from year-to-year). In these DSEM models we simultaneously estimate the mean, trend, autoregression, and residual standard deviation (see [25, 68], or [7] for more details). Moreover, each of these parameters is estimated as a random effect (i.e., as varying between individuals) and compared to a model with fixed effect parameters (i.e., assumed constant between individuals). One central expectation is that within person fluctuations are not (solely) measurement error, which we would expect to be similar across individuals. Instead, we hypothesise that within-person variability reliably differs between individuals for a given dataset with suitable temporal resolution. As such, our first hypothesis is that*Hypothesis 1.1: A DSEM with a parameter estimating the variance of subject-specific deviations in trial-to-trial variability will be preferred over a model that omits it, across all tasks.**Hypothesis 1.2. A DSEM with a random-effects structure that freely estimates variability in mean performance from day-to-day (or session-to-session) will be preferred, over a model that only estimates fluctuations at faster timescales.*

Second, we expect that individual differences in variability will be correlated across tasks, but more weakly so than individual differences in (average) performance. Moreover, we expect that these differences cannot be fully captured with a single latent factor [7]. As such, our second preregistered prediction is as follows*Hypothesis 1.3: After extracting individual-level estimates of variability, we will fit a single factor model of variability across the 5 tasks, separately for each timescale. This unidimensional model will not fit sufficiently well (as indexed by a significant chi-square and an RMSEA* > *0.05). This prediction will hold for each timescale (trials, sessions, days).*

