Additionally, we study the role of psychological (e.g., mind wandering, sleep, mood) and environmental (e.g., socio-economic status (SES)) factors on between- and within-person differences in variability by using them as predictors in a (regularised) SEM.*Hypothesis 2.8: Individuals from lower SES backgrounds will show greater day-to-day variability.**Hypothesis 2.9: Individuals with greater mind wandering tendency will show greater cognitive variability, especially at the trial-to-trial level.**Hypothesis 2.10: Days or testing sessions with greater negative affect, poorer sleep, and/or more background noise will be days or testing sessions with greater variability as well as poorer mean performance.**Hypothesis 2.11: Tasks ranked as less enjoyable (individually) will be tasks with greater variability as well as poorer mean performance (when adjusting for task difficulty).*

To understand variability within individuals, we have to consider not only unique within-subject predictors but also potential subgroup differences. Neubauer et al. [43], identified subgroups of different profiles within a population for whom mood had varying effects on variability (i.e., low mood leading to higher variability, high mood leading to higher variability, mood having little effect on variability, and a group where both low and high mood lead to higher variability). We will use mixture models to identify subgroups within the population, allowing for the coupling of variability with factors like mood, sleep, background noise, and motivation (task rank). Specific subgroups that will be identified due to interactions between these factors are mostly exploratory, as not enough research has investigated this question so far.*Hypothesis 2.12 (exploratory): The overall sample will consist of a mixture of distinguishable subgroups in the population with a subgroup having a negative impact of mood, sleep quality, background noise, and motivation (task ranking) on variability and a subgroup having no negative impact of mood, sleep, background noise, and motivation (task ranking) on variability.*

The parents or guardians of the subgroup taking part in the imaging study are also asked to perform the cognitive tasks on tablet at each session. These scores act as predicting variables in latent mixed models to explore possible hereditary correlations.*Hypothesis 2.13: Variability will be correlated between parents and children*

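### Hypothesis 2.11 compares variability between five differently built tasks and adjusts only for task difficulty, so a shared liking for some games can pass for an effect of individual enjoyment

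*Protocol article*

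**What the plan says.** Under Statistical analyses, Key hypotheses, Aim (2), Hypothesis 2.11 reads: "Tasks ranked as less enjoyable (individually) will be tasks with greater variability as well as poorer mean performance (when adjusting for task difficulty". The rationale, under Psychological factors, Motivation, is that if enjoyment governs variability, a child's ordering of the tasks by fun "would correspond to a similar, scaled ordering of variability". The scaling is not defined.

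The model for this group of predictors is described as "using them as predictors in a (regularised) SEM". Variability comes from dynamic structural equation models, of which Aim (1) says "we simultaneously estimate the mean, trend, autoregression, and residual standard deviation".

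Cognitive tasks describes five different formats:
- Processing speed: "A mole disappears once it is pressed or after 2000ms".
- Fluid reasoning, behavioural arm: "there is a time limit of 30 s on the response".
- Vocabulary: "There is no time limit on each trial".
- Working memory: the span adapts to the child.
- Exploration: no points are given for speed.

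Performance is recorded as binary or continuous, and response time is recorded for every task. Each child orders the five tasks by fun after 10 sessions.

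**The concern.** A residual standard deviation carries the units and range of its outcome. A response time that cannot exceed 2 s and one with no upper limit need not have similar spreads in any child, however motivated. Ordering tasks by this quantity therefore mixes format with behaviour.

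Enjoyment may also differ between tasks on average. If some games are generally more popular, the same alignment between popularity and format-driven spread recurs in every child. Six hundred children then repeat one comparison of five tasks and do not replicate it independently. The question of interest is whether a child who likes a task less is more variable on it. The question tested would partly be whether popular games happen to have small spreads.

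Difficulty is a different property from timing scale, so a difficulty score need not remove this. The wording also allows the adjustment to attach only to mean performance, which would leave variability with none. At stake is one of the 23 key preregistered predictions. Task rank is also used again in the mixture models of Hypothesis 2.12.

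**Working it through.** **Nearest stated figure.** The article gives no power or error figure for Hypothesis 2.11. Under Sample size considerations, Behavioural arm, it gives r = 0.11 at 80% power for N = 600. With the Fisher transformation and two-sided alpha 0.05 (assumed), r = tanh((1.960 + 0.842)/√597) = tanh(0.1147) = 0.114, which agrees after rounding.

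**Where the false association comes from.** For child i and task t, suppose individual enjoyment has no effect:
- log variability: y = a_i + τ_t + e_it, where τ_t is the task's fixed level;
- rank: R = ρ_t + r_it, where ρ_t is the task's average rank.

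Regressing y on R within child, without a task term, gives in expectation

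β = [(1/5) Σ (τ_t − τ̄)(ρ_t − ρ̄)] / 2,

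because the ranks 1 to 5 have variance (4+1+0+1+4)/5 = 2 within every child. This is zero if all ρ_t are equal (no shared preference) or all τ_t are equal (same spread in every task). Otherwise it is generally not zero, and it does not shrink as children are added, whereas its standard error does. A fixed effect for each task removes τ_t and hence β. The same algebra holds for mean performance.

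**Null simulation.** There were 400 simulated studies per cell, 600 children and five tasks. The outcome was log residual SD, with child effects and child-clustered standard errors. Assumed inputs, none from the article:
- task SDs of 0.3, 1, 1, 5 and 4 s (5/0.3 ≈ 17-fold), or of 0.8 to 1.2 (1.5-fold), or equal;
- child-level and residual SD of 0.3 on the log scale;
- shared preference in units of the individual liking SD;
- difficulty as a per-child, per-task error rate.

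For 5% the simulation error is 1.96 × √(0.05 × 0.95/400) ≈ 0.02. Two-sided rejection rates:

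| Task SDs | Shared preference | No task term | Difficulty covariate | Task fixed effects |
|---|---|---|---|---|
| 17-fold | none | 0.06 | 0.05 | 0.07 |
| 17-fold | 0.1 | 0.99 | 0.97 | 0.06 |
| 17-fold | 0.3 | 1.00 | 1.00 | 0.05 |
| 1.5-fold | none | 0.04 | 0.05 | 0.07 |
| 1.5-fold | 0.1 | 0.63 | 0.42 | 0.05 |
| 1.5-fold | 0.3 | 1.00 | 1.00 | 0.04 |
| equal | 0 to 0.6 | about 0.05 | about 0.05 | about 0.05 |

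In these rows the less-liked tasks were given the larger SDs, which is the unfavourable alignment. With the liking order random relative to the 17-fold SDs, rates were (predicted direction in brackets):
- shared preference 0.1: 0.51 (0.27) with no task term, 0.44 (0.23) with the difficulty covariate, 0.07 with task fixed effects;
- shared preference 0.3: 0.80 (0.37), 0.79 (0.38) and 0.06.

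A wider grid at N = 600, with task levels and liking drawn at random, used a between-task SD of log variability of 0.15 to 0.7 and a shared-liking SD of 0.1 to 1.0. It gave about 12 to 90% with a difficulty covariate, even where difficulty was correlated with task spread, and 3 to 7% with task fixed effects.

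**More children do not help.** In the 17-fold, 0.1 case the mean test statistic rises from 2.5 at N = 200 to 4.4 at N = 600. The ratio is 4.4/2.5 = 1.76, close to √(600/200) = 1.73, as expected of a constant bias.

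**The case against.** The article nowhere says that raw standard deviations are pooled without a task term. It names a structural equation model and an adjustment for difficulty, and it points to preregistered analyses that are not shown. With five fixed tasks, task intercepts are an ordinary way to adjust for difficulty. If each task's variability is a separate variable in the model, each has its own intercept and the problem goes. The clock argument also bears mainly on response times, and the hypothesis does not say which outcome it uses. The word scaled in the rationale suggests some rescaling. All of this stands as a limit on how strongly the point can be put.

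It does not remove the point. Task intercepts would take out the very ordering between tasks that the hypothesis and its rationale announce, so the published wording would then describe a different test from the one run. Pooling binary and continuous outcomes would not make the standard deviations comparable either.

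A reader might infer that differing clocks alone produce a significant result, or that overall popularity of the games decides the outcome. The documents do not support that. Without a shared preference, rejection stays near 5% even with 17-fold differences in spread, and the article reports no rankings. Nor is the bias bound to favour the hypothesis: it can equally oppose it.

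**Conclusion.** The point holds in conditional form. As worded, Hypothesis 2.11 compares tasks whose spreads can differ by format, and the one adjustment named is undefined and may not cover variability. If task spreads differ and children share some preference, false rejection with a difficulty covariate is about 12 to 90% two-sided at N = 600. Roughly half of that is in the predicted direction, against a nominal 2.5% on that side. Task fixed effects bring the two-sided rate back to about 5%.

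The size rests on assumed task spreads, degrees of shared preference, a two-sided alpha of 0.05, and difficulty entering as a covariate. If the unseen preregistration codes difficulty as task intercepts for both outcomes, the analysis is sound and only the published wording needs correcting. The change is worth making before the hypothesis is tested. It concerns one prediction among 23 and does not touch the study's design.

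**What to change.** State Hypothesis 2.11 as a within-task test. Put all child-by-task values in one model with a fixed effect for each task, a child effect and the child's own rank. Take variability on the log scale or standardised within task. Say that the task effects are how difficulty is adjusted for, and that this applies to both variability and mean performance. The test is then whether children who rank a given task lower than other children do are more variable, and perform worse, on that same task. Report the ordering between tasks described under Motivation descriptively only, since it rests on five tasks.

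The cost is four task indicators and a wording change in the preregistration; no new data are needed. The downside is a narrower estimand: the part of the ranking that children share no longer counts as evidence for the hypothesis.

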### Sample size considerations

#### Behavioural arm

The number of subjects needed in DSEMs have previously been examined through a series of Monte Carlo simulations [126]. Focusing on univariate two-level autoregressive models, they demonstrate that the DSEM performs well across a range of scenarios. For example, the estimation stability gained from a larger number of subjects is greater than the benefits of a large number of trials. Crucially, they demonstrate that DSEM achieves a highly reliable estimate of individual differences in trial-to-trial cognitive variability with anywhere upwards of 15 trials, given 200 subjects (average estimate over 500 repetitions/true value = 0.88, [126]).

In terms of power to detect significant associations, the behavioural arm of the CODEC study is effectively at ceiling (see Fig. 9) for effect sizes we observe in previous literature, including the effect of mind wandering on variability (*r* = -0.53, 100% power; [52]), variability on ADHD symptoms (*r* = 0.39, 100%; [94]), and inattention on variability (*r* = 0.24, 100% power; [19]). For the full behavioural sample (*N* = 600), even small effect sizes (*r* = 0.11) can be detected with 80% power.

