Individuals willing to take part in the study, but whose school/classroom does not or cannot participate, can be recruited on an individual basis. The parents/guardians who have expressed interest in participating receive a dedicated informed consent and information sheet either in person, by post or email, depending on their preference. Parents or guardians of participants are asked to give, or decline, consent for 1) participation in the behavioural study, and additional consent 2) to be contacted to receive more information about the imaging study, 3) for the researcher to obtain Cito scores (or equivalent academic results) through the school (only for those children recruited in classrooms), and 4) to be contacted to receive more information for other follow-up studies. Agreeing to 1 is possible without agreeing to 2, 3 and/or 4. For participants consenting to be contacted for the imaging study or follow-up studies, the preferred means of communication (phone or email) is requested, and the relevant information provided. Parents are contacted through their preferred means of communication (either through post, email or in person) and receive the information sheet and informed consent for the imaging part (if agreed upon). Parents or guardians give consent on the ‘imaging’ informed consent form to have their child take part in the imaging study (CODEC-MRI). An additional informed consent form asks parents/guardians to perform the cognitive battery tasks, identical to the tasks performed by the child in the behavioural study and/or to respond to a set of questionnaires on their child and their environment. Parental participation is not necessary for the child to enrol in CODEC-MRI. A new consent form needs to be signed for the child to take part in the second MRI scan and for the parents/guardians to take part in the second accompanied behavioural tasks and questionnaires. 

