#### Imaging assessment

Before the imaging session in the scanner, children perform each of the five original cognitive tasks as used in the behavioural part for 3 min (15 min) and the child participants finish a set of tailored questionnaires and tasks. These are:*A digital mood scale:* a smiley question that assesses the child’s mood. The smiley changes along with the slider and ranges from an unhappy or sad smiley to a happy or joyful smiley. The number indicated by the slider ranges from 0 (unhappy smiley) to 100 (happy smiley).*A digital sleep scale*: a question that assesses the child’s sleep the evening before the session. The icon ranges from a bad night’s sleep (0) to a good night’s sleep (100).*Highly Sensitive Child scale – short form:* the HSC is a 12 item self-report scale (from 1-strongly disagree to 7-strongly agree) measuring environmental sensitivity. This scale has good internal consistency in children as young as 8 years ([109], for the Dutch version see [110]).*Mind Excessively Wandering Scale*: The MEWS is a 12 item self-report measure rating items on a scale from 0 (not at all or rarely) to 3 (nearly all of the time or constantly). The MEWS has an acceptable internal consistency in both adults and children from 8–13 years [111].*Alternative uses tasks:* children are asked to produce as many alternative uses for five physical objects (cap/hat, pen, cloth hanger, spatula, and a towel) for 2 min per object, based on Van Dijk et al. [112]. The experimenter reports the responses on a tablet, either by indicating one of the responses identified as an unoriginal answer in the study by Van Dijk et al. [112] or by writing out the answer. Fluency, flexibility, and originality are calculated.

During the imaging session, two blocks of fluid reasoning (2*8,5 min each) are performed by the child, one with low time constraints (30 s) and one with high time constraints (10 s). The time constraints are known to induce different task strategies which is a key variable of interest [66]. During the two task blocks, we record response time, accuracy, gaze direction, and pupil dilation (through the Eyelink 1000 Plus eye-tracking system). This requires a brief period of calibration (2 min) at the start of each fMRI task block.

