Additionally, accompanying parents who agree perform a cognitive task battery identical to the one used in the behavioural arm for children and respond to a set of questionnaires about their child at each session. The set of questionnaires consists of:*Socio-demographic questionnaire:* a 15-item questionnaire assesses the child’s age, sex, handedness, grade, and the first and second language as well as the parents’ postal code, highest level of education attained, and job type and status.*Strengths and Difficulties Questionnaire*: the SDQ is a 25 item scale rating items from 0–2 (0-not at all/only a little, 1-quite a lot, 2-a great deal) providing a total difficulty score and five subscales consisting of five items each (hyperactivity, conduct problems, peer problems, emotional symptoms and prosocial). The parent-report scale has acceptable internal consistency [113].*MEWS:* the 12 item self-report scale assesses mind wandering and has good internal consistency in adults [114].*Behaviour Rating Inventory of Executive Function 2*: the BRIEF-2 is a questionnaire completed by parents to measure a child’s daily behaviour related to executive functions with good internal consistency [115].

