**Aim (2) Underlying mechanisms:** in the imaging arm, we consequently use key predictors of interest in the deeply phenotyped subsample (*N* = 200) to test mechanistic hypotheses about the (hypothesised) causes of individual differences in variability. In terms of brain structure, we first test the known association between larger grey matter volume and better cognitive performance to replicate previous findings [124]. Then, we test the neural noise hypothesis, which suggests that better myelination of the brain is associated with less variability due to decreased signal loss [73].*Hypothesis 2.1: Children with larger grey matter volume will demonstrate better cognitive performance in the behavioural tasks.**Hypothesis 2.2: Children with larger white matter volume (better myelination) will demonstrate higher BOLD signal variability (potentially reflecting lower neural noise).**Hypothesis 2.3: Children with higher tract-based indirect measures of myelination (both in white matter tracts and in grey matter) between frontoparietal executive systems (specifically: the SLF, ATR, IFOF and Forceps Minor) will show less variability. This effect will manifest most strongly for complex tasks, as those are most dependent on multi-region information integration.**Hypothesis 2.4: Myelination increases during childhood. Children with steeper increase in myelination (both in white matter tracts and in grey matter) will show sharper decrease in behavioural variability between year 1 (*~*8 years old) and year 3 (*~*10 years old).*

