**Fig. 9 Fig9:**
[figure not shown]
Power analysis based on our baseline sample size (600) and effects observed in our pilot analyses: A strong association between mind wandering and variability (*r* = -0.53), a moderate association between variability and ADHD (*r* = 0.39), and a small to moderate association between variability and inattention (median *r* = 0.24)

Our sample size of 600 children consists of children tested in schools and on an individual basis at home. By including participants that are recruited individually and tested at home, we add a new variable of a situational context. This enables us to test potential differences in cognitive variability between school and home environments. Factors such as systematic differences, the role of self-initiating sessions, the absence of peer influence, and variations in noise levels between both contexts are likely to have distinct impacts on cognitive variability. To ensure sufficient power for each group, we hope to recruit at least 135 participants tested at home, allowing us to both ensure precision of parameter estimation within each group (home and school based), as well as detect the hypothesised effect size group difference between the two with > 80% certainty (see Fig. 10).

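### The 100% power figures for mind wandering, ADHD symptoms and inattention are computed at N = 600, but the scales for these constructs are given only in the imaging arm of about 200 children

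*Protocol article*

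**What the plan says.** Under Sample size considerations, Behavioural arm, the protocol article states that "the behavioural arm of the CODEC study is effectively at ceiling (see Fig. 9) for effect sizes we observe in previous literature". Three associations follow, each with 100% power: mind wandering with variability (r = -0.53), variability with ADHD symptoms (r = 0.39), and inattention with variability (r = 0.24). The Fig. 9 caption fixes the sample: "Power analysis based on our baseline sample size (600) and effects observed in our pilot analyses". The paragraph closes by saying that, for the full behavioural sample of 600, "even small effect sizes (*r* = 0.11) can be detected with 80% power".

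The measurement schedule is set out elsewhere:

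- **Behavioural arm.** The Behavioural assessment section lists the five tasks, background noise, mood and sleep sliders, a ranking of the tasks by enjoyment, academic results where consent is given, and basic demographics. It lists no scale for mind wandering, ADHD symptoms or inattention.
- **Child mind wandering.** The MEWS is in the Imaging assessment section: "The MEWS is a 12 item self-report measure rating items on a scale".
- **ADHD-type symptoms and inattention-type behaviour.** The SDQ, with its hyperactivity subscale, and the BRIEF-2 are in the same section. They are completed by accompanying parents who agree to take part and who "respond to a set of questionnaires about their child at each session". The Study population section likewise directs the parent questionnaires to the imaging subgroup.
- **Size of that subgroup.** The Study population section expects about one third of 600, that is 200. Under Recruitment and enrolment, "Parental participation is not necessary for the child to enrol in CODEC-MRI".

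**The concern.** The power statement and the measurement schedule do not fit together. Power for an association depends on the number of children who have both variables. Variability is measured in all 600, but the other variable in each of the three examples is measured in about 200, or in fewer where it depends on a parent. All three examples offered for the 600-child arm therefore use a sample size that the design does not deliver for them. The section gives no example for a predictor that all 600 children have.

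The constructs matter because mind wandering is the subject of Hypothesis 2.9 and ADHD symptoms of Hypothesis 3.5. A reader who takes the behavioural-arm paragraph at face value would judge those hypotheses against three times the children actually available, and would think the sensitivity to small effects better than it is.

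**Working it through.** **Inputs**

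- r = 0.53, 0.39 and 0.24 (absolute values), N = 600, and detectable r = 0.11 at 80% power: Behavioural arm paragraph and Fig. 9 caption.
- N = 200 for the imaging arm: Study population section, as an expectation (600 × 1/3).
- Significance level: not stated in this section. Two-sided 5% is assumed, so z = 1.960; z for 80% power = 0.842.
- Number with a participating parent: not stated. A range of 100 to 180 is shown as an assumption.

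**Formulas**

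Power ≈ Φ(atanh|r| × √(N − 3) − 1.960); the opposite tail is negligible here.

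Detectable r at 80% power = tanh((1.960 + 0.842) / √(N − 3)).

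**Step 1. The plan's own figures at N = 600** (√597 = 24.43)

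- r = 0.24: 0.2448 × 24.43 = 5.98; 5.98 − 1.96 = 4.02; power 100%.
- r = 0.39 and r = 0.53 lie further out; power 100% for both.
- Detectable r: tanh(2.802 / 24.43) = 0.114, which rounds to the stated 0.11.

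The stated figures reproduce, so the arithmetic is sound for N = 600.

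**Step 2. The same associations at N = 200** (√197 = 14.04)

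| Association | r | atanh r × √197 | minus 1.96 | Power at N = 200 | Stated |
|---|---|---|---|---|---|
| Mind wandering | 0.53 | 8.28 | 6.32 | >99.99% | 100% |
| ADHD symptoms | 0.39 | 5.78 | 3.82 | 99.99% | 100% |
| Inattention | 0.24 | 3.44 | 1.48 | 93.0% | 100% |

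A simulation with 20,000 replicates gave 93.1% for r = 0.24. Detectable r at N = 200 is tanh(2.802 / 14.04) = 0.197. A true r of 0.11 would have 34% power.

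**Step 3. Fewer children with parent report**

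This applies to the SDQ and BRIEF-2. The child MEWS is self-report and does not depend on the parent.

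| N with parent report (assumed) | Power, r = 0.24 | Power, r = 0.39 | Detectable r at 80% |
|---|---|---|---|
| 180 | 90.3% | 99.98% | 0.208 |
| 150 | 84.3% | 99.9% | 0.227 |
| 135 | 80.3% | 99.7% | 0.239 |
| 120 | 75.4% | 99.4% | 0.253 |
| 100 | 67.4% | 98.2% | 0.277 |

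Power for r = 0.24 stays at 80% or more while at least 135 of 200 children (135/200 = 67.5%) have a participating parent.

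**The case against.** The strongest reply is that little changes at the quoted effect sizes. Two of the three associations stay at about 100% at N = 200, the third is still at 93%, and it keeps 80% down to 135. The Imaging arm paragraph already gives the sensitivity at N = 200 (over 80% at r = 0.2 and over 99% at r = 0.3), and both figures reproduce (81.2% and 99.1%). That stands, and it limits the size of the problem. It does not remove it: the imaging paragraph illustrates its power with neural data only and does not mention these three associations, which remain assigned to N = 600.

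A reader might also infer more than the documents support:

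- **That the ceiling claim fails for all three.** Only inattention leaves the ceiling.
- **That Hypotheses 2.8, 2.9 and 3.5 are presented as powered for r = 0.11.** The r = 0.11 sentence is limited to the full behavioural sample and names no hypothesis. Socio-economic status does not appear in the power text.
- **That r = 0.11 has 77% power and not the stated 80%.** At exactly 0.11 the two-sided figure is 77.0%, but 0.114 gives 80% and rounds to 0.11. One-sided 5% would give 85.4% at 0.11, and the sidedness is not stated. This is rounding.
- **That Aim 2 itself assigns N = 200 to these predictors.** Its opening says "we consequently use key predictors of interest in the deeply phenotyped subsample", but that text does not name mind wandering, ADHD symptoms or inattention. Aim 2 also holds Hypotheses 2.10 and 2.11, whose measures are taken in all children.
- **That power for Cito scores is misstated.** These scores are sought only for classroom recruits, but the section states no power for them, so no figure is wrong.
- **That 200 is a ceiling.** The text gives it as an expectation.

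**Conclusion.** The concern holds as a misattributed sample size. The three associations used to show the power of the 600-child arm can be tested only in the imaging arm, in about 200 children, and in fewer for the two that rest on parent report. Corrected power is about 100%, 100% and 93%, and the detectable correlation is about 0.20 in place of 0.11. With parent report in an assumed 150 children, r = 0.24 has about 84%; at 135 it has 80%.

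This is a moderate internal inconsistency. Power at the quoted effect sizes remains adequate unless parent participation falls below about two thirds of the imaging arm, and the documents give no reason to expect that.

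The figures assume two-sided 5% and simple correlations, and take no account of attrition, classroom clustering or multiplicity. The imaging arm also excludes children with a psychiatric history or past psychotropic medication. That may narrow the range of ADHD symptoms, but the documents do not allow the effect to be quantified.

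**What to change.** 1. Move the mind wandering, ADHD symptom and inattention examples from the behavioural-arm paragraph to the imaging-arm paragraph, and restate their power at N = 200 as about 100%, 100% and 93%.
2. Redo Fig. 9 at N = 200, with a second scenario for reduced parent participation (for example 150, giving about 84% at r = 0.24), and state the significance level and sidedness.
3. Keep r = 0.11 (more precisely 0.114) at N = 600, and say that it applies only to measures taken in all children: the tasks, mood, sleep, noise and task ranking.

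The cost is one reworded paragraph and one redrawn figure. Design, recruitment target and hypotheses are untouched. The only downside is that the inattention figure becomes slightly less favourable.
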